### Sample size calculations

The sample size calculation will be based on a mean difference in the length of hospital stay of 2.5 days; considering a confidence interval of 95%, power of 80%, and a ratio of 1: 1 between the two groups. Based on the averages of the study by Dong et al. [33] (12.7±4.1 vs 15.2±4.5 days), a sample size of 94 patients was obtained, 47 for each group. After adjusting 20% for missing, death, loss to follow-up, and withdrawals, the corrected sample was 118 subjects. The study by Dong et al. [33] was chosen because it had a population similar to that in the present study. Among other aspects of population similarity, the study involved patients able to perform activities independently and with a probability of <50% for death at 6 months. The sample size calculation will be performed using the module that calculates sample sizes to compare two averages available on the website: https://www.openepi.com/SampleSize/SSMean.htm.

This sample also will be sufficient to contemplate the functional independence objective, based on the percentage of patients returning to their functional state at the time of hospital discharge (FSS = 35). A final sample size of 86 patients was obtained, 43 for each group, based on 50% of patients returning to the previous functional state at the time of hospital discharge [34] and assuming that 80% of the patients remained in the intervention group at the time of hospital discharge.

### Data analysis

For the analysis of demographic and clinical data, descriptive statistics will be used. The data of continuous variables will be analyzed with measures of central tendency and dispersion. The categorical variable data will be analyzed with frequency measurements. To perform the inferential statistics, tests for normality and homogeneity of variance will be performed. Since the data will be normally distributed, analysis of variance (ANOVA) will be used to compare the mean differences of the variables, followed by the Bonferroni post hoc test. If there will be no normal distribution, the Kruskal-Wallis test will be used, followed by the Mann-Whitney post-hoc test. χ2 tests will be used to evaluate the differences in the categorical variables between the groups.

Kaplan-Meier analysis will be used to estimate ICU LOS, mortality, and mechanical ventilation time, and a log-rank will be used to assess the difference between the groups. Poisson or negative binomial model will be used to estimate the incidence rate ratio. Stratified analyses will be performed according to age, initial functional status, and the Acute Physiology and Chronic Health Enquiry (APACHE-II) score to identify potential confounders. Cohen's *d* effect sizes will be also calculated. Before carrying out the analyzes, test methods assumptions will be verified.

Mean and median differences and 95% confidence intervals will calculated. The significance threshold will be used *P* < .05 for each outcome and testing will be used two-sided. The statistical software used will be used IBM SPSS for Windows 21.0. All study analyses will be used performed according to the intention to treat.

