### Intervention outcomes

Socio-demographic, health, and lifestyle data will be collected from the patients through the report of the legal guardians and when possible, the patients themselves. Data of the medical aspects of the study will be collected through the patient's chart, ICU monitors, and direct communication with the multidisciplinary team. The data will be recorded in an appropriate form by properly trained researchers. Researchers who collected study data will not be part of the hospital staff.

All outcomes will be assessed according to the outcome assessment recommendations of Young et al. [25]. The primary outcome will be the length of stay in the ICU. The secondary outcome measures included:

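### ICU stay is sized as a difference in means, but the only test named for it is the log-rank and no test is designated as deciding, so the stated 80% power is not established for the named test

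*Protocol article*

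**What the plan says.** All places are in the Protocol article, Methods.

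- **Intervention outcomes:** "The primary outcome will be the length of stay in the ICU".
- **Sample size calculations:** the number comes from a web "module that calculates sample sizes to compare two averages", with 95% confidence, 80% power and 1:1 allocation. Inputs and result are "12.7±4.1 vs 15.2±4.5 days), a sample size of 94 patients was obtained, 47 for each group", raised to 118 for an assumed 20% loss. The section states the effect as "The sample size calculation will be based on a mean difference in the length of hospital stay of 2.5 days". That label (hospital, not ICU) is a separate matter; here the figures are taken as intended for the primary outcome.
- **Data analysis, first paragraph:** after tests of normality and equal variance, "Since the data will be normally distributed, analysis of variance (ANOVA) will be used to compare the mean differences of the variables". If the data are not normal, Kruskal-Wallis followed by Mann-Whitney replaces it. The rule is general. It neither names nor excludes ICU stay.
- **Data analysis, second paragraph:** ICU stay is listed by name under Kaplan-Meier estimation, together with mortality and ventilation time, and "a log-rank will be used to assess the difference between the groups". This is the only test attached to ICU stay by name. The next sentence, "Poisson or negative binomial model will be used to estimate the incidence rate ratio", names no outcome.
- **Data analysis, third paragraph:** both mean and median differences with 95% intervals are promised, without saying which belongs to which outcome. The sentence opening "The significance threshold will be used" sets two-sided P < .05 for each outcome.

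**The concern.** A two-mean calculation fixes the power of a t-test (or ANOVA, which is the same test with two arms). It does not fix the power of a log-rank test, which depends on how the discharge hazards of the arms compare over time. The article gives no hazard ratio, event count or distribution of stays from which log-rank power could be read, so its 80% is a statement about one test while the outcome is assigned by name to another.

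The general rule for continuous variables adds a second P value for the same outcome, and the threshold is set per outcome without saying which P value it applies to. Two things are at stake: whether the trial has the power it claims for the analysis it names, and whether the conclusion on the primary outcome could turn on a choice of test made after the data are seen.

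**Working it through.** **1. Reproduce the plan's figure.** Inputs from Sample size calculations: difference 2.5 days, SDs 4.1 and 4.5, two-sided 5%, power 80%.

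n per arm = (1.960 + 0.842)² × (4.1² + 4.5²) / 2.5² = 7.849 × 37.06 / 6.25 = 46.5, so 47 per arm and 94 in all. Then 94 / 0.8 = 117.5, so 118 (59 per arm). Both stated figures reproduce. Power of the two-mean comparison at 47 per arm is 80.4%.

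**2. Power of the log-rank with the same inputs.** The article gives no distribution, so three shapes were assumed, each with the stated means and SDs: normal, gamma (shape = (mean/SD)², i.e. 9.60 and 11.41) and log-normal (log-variance = ln(1 + (SD/mean)²)). Results come from at least 4,000 simulated trials per shape, two-sided 5%. The figures below allow for about one percentage point of variation between runs.

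| Setting | Normal | Gamma | Log-normal |
|---|---|---|---|
| ANOVA / t-test, 47 per arm | about 80% | about 80% | about 80% |
| Log-rank, 47 per arm, no censoring | 80–81% | 70–72% | 70–71% |
| Log-rank, 59 per arm, no censoring | 87–89% | about 80% | about 80% |
| Log-rank, 59 per arm, 20% censored at random during stay (assumed) | 82% | 75% | 71% |

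The loss under skew has a simple source. In the gamma case the discharge hazards for long stays tend to 9.60/12.7 = 0.756 and 11.41/15.2 = 0.751 per day, a ratio of about 1.01. The log-rank gives those late discharges full weight although they carry almost no contrast.

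In the two skewed shapes about 60 evaluable patients per arm are needed for 80% log-rank power, against 47 evaluable and 59 randomised per arm in the plan.

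**3. Error rate if either test may claim success.** Both arms were given mean 15.2 and SD 4.5, with 47 per arm. The gate was taken as a Shapiro-Wilk test at 5% in each arm (an assumption, as the article names no normality test), leading to ANOVA or, failing it, the rank test.

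- Gated test alone: about 5% (4.6–5.5%).
- Log-rank alone: about 5.5%.
- At least one of the two significant: about 6–8%.

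The tests are strongly correlated, so this lies below the 1 − 0.95² = 9.75% that two independent tests would give.

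**4. How often the choice decides the conclusion.** Under the planned effect at 47 per arm, the log-rank and the gated test fall on opposite sides of P = .05 in about 10% of trials (normal) to about 15% (log-normal).

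**The case against.** The strongest reply has four parts.

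- *Power need not be short.* Under normality the log-rank has about 80% power, and if all 118 contribute uncensored stays it has about 80–89%. Gamma and log-normal shapes are not in the article. This stands. A reader might infer that the trial is underpowered; the documents do not show that. They show only that the 80% was not derived for the named test.
- *The error inflation supposes selective use.* ANOVA and Kruskal-Wallis are alternatives, not two extra tests, and the threshold is stated per outcome. This stands too: with one test fixed in advance the error stays near 5%, and 6–8% arises only if either result could be claimed. Nothing in the article excludes that.
- *The count model and post hoc steps may have other uses.* The Poisson or negative binomial model has no named outcome and could be meant for the incidence of ICU-acquired weakness. The post hoc tests could serve the repeated ultrasound and strength measurements. A reader might count them as further tests of ICU stay, or as redundant with two arms, but the text does not support either reading. Likewise, the opening word of the ANOVA sentence probably means *if*, since a non-normal branch follows; it should not be read as a claim that stays are normal.
- *Naming a primary test is often left to a fuller document.* That covers missing detail. It does not cover an article that states both a sample-size method and a named test for the primary outcome when the two do not match.

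**Conclusion.** The point holds in a limited form and should be fixed. The primary outcome is sized on a comparison of means and assigned by name to a log-rank test. A general normality-gated rule also covers it, and nothing says which result decides.

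It would go too far to say that neither the 80% power nor the 5% error rate holds. What the article supports is that neither is assured. At 94 evaluable patients the log-rank has about 80% power if stays are normal and about 70–72% if they are right-skewed; using all 118 moves this up or leaves it similar, depending on how many stays are censored. The type I error is about 6–8% only if success may be claimed on either test. The disagreement in roughly 10–15% of trials is the practical reason to settle the choice in advance.

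These sizes rest on the article's means and SDs applying to ICU stay, and on assumed shapes, censoring and normality test.

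**What to change.** Before unblinding, name one primary test and one matching effect measure for ICU stay. Either route works:

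- **Comparison of means,** as sized: difference in mean days with a 95% interval and no normality gate for this outcome. The stated power then applies as it is.
- **Log-rank or Cox model:** hazard ratio with a 95% interval and a stated handling of deaths in the ICU. Power should then be restated as about 70–80% at 94 evaluable patients, with the assumed distribution and loss shown.

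In both cases, label every other analysis of ICU stay as supportive, with no significance claim on the primary outcome.

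The cost is a few sentences and, on the second route, a stated power that may be slightly less favourable. No extra patients are needed.

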### Participants

Patients admitted to the ICU of the Universitary Hospital [name] of the Federal University of Bahia (UFBA), Salvador, Bahia, Brazil, who met the eligibility criteria will be recruited in the study. Inclusion criteria: Patients hospitalized in the ICU aged 18 years or more with the following: a minimum functional classification of level 1 (i.e. being able to roll in the bed and bridge); Barthel index [11] recall of at least 70, 2 weeks prior to ICU admission [12]; and the ability to interact with the physiotherapist, determined by at least three positive responses of the following five commands: (1) “Open (close) your eyes,” (2) “Look at me,” (3) “Open your mouth and put out your tongue,” (4) “Nod your head” and (5) “Raise your eyebrows when I have counted to five" [13].

Exclusion criteria included the following: patients with hospitalization time greater than 72 hours before the start of the study; patients with an estimated mortality rate greater than 50% according to Acute Physiology and Chronic Health Disease Classification System II (APACHE II) [12]; patients with increased intracranial pressure or with an history of cardiorespiratory arrest; patients with unstable fractures that hamper the progression of mobilization levels; lower limb amputees; patients with degenerative neuromuscular disease; and those with a history of cerebrovascular accident, traumatic brain injury, or radiotherapy and/or chemotherapy in the last 6 months.

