Cross-sectional area and muscle thickness of the rectus femoris and biceps brachii measured by ultrasound, using an 8-MHz 5.6-cm linear transducer array (PLM805, Toshiba Medical Systems, Crawley, UK) immediately after randomization and at intervals of 48 h for 28 days or till discharge from the ICU, whichever occurred earlier. For evaluation of the rectus femoris, the transducer will be placed perpendicular to the long axis of the thigh on its superior aspect, three-fifths of the distance from the anterior superior iliac spine to the superior patellar border [26]. Biceps brachii will be evaluated at the midline between origin and insertion [27]. The transducer will be positioned with slight pressure.Change in muscle strength will be evaluated immediately after randomization, after 3 days and at intervals of 7 days, up to the 28th day or till discharge from the ICU. Muscle strength will be measured using the following: (1) Medical Research Council sum-score (MRC) [28]; (2) handgrip, using a hydraulic dynamometer (Saehan Corporation SH5001, Korea), with the handle pressed for at least 6 seconds in three trials with a 1-min intervals; the highest value of manual grip strength in kilograms (Kgf) will be considered for the analysis [29]; (3) hand-held dynamometer of elbow flexion and knee extension (model 01163; Lafayette Instrument, Ind) [30]; and (4) five Sit to Stand Tests [31].Functional status at 28 days after randomization or discharge from ICU will be measured using the FSS [23], Surgical Optimal Mobilization Score (SOMS) [12], and timed up-and-go score [32].ICUAW will be determined by a score lower than 48 on the MRC sum-score, according to Vanpee et al. [28].Days with mechanical ventilation and mortality at 28 days after randomization or discharge from the ICU.

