### Strengths and weaknesses of the study

One of the strengths of the study is the study design, which involved blinding of the patients and functional assessors, presenting an adequate sample for the proposed objectives as well as an adequate description of the interventions offered in both groups. Recently, a Cochrane review [4] described that there is insufficient evidence of good quality to support the benefits of mobilization for improved physical function or performance, muscle strength, and quality of life. The present protocol, based on an individualized prescription and focusing on transference and locomotion, as well as on the monitoring of effort intensity (using the Borg scale), may expose patients to an adequate dose so that the effects of exercise can promote the necessary changes in the cardiorespiratory system and skeletal muscle. Another important point is that the protocol will have an early start and will be based on active mobilization, which will reduce some confounding variables observed when this mobilization is initiated at a later stage.

The protocol has some limitations, such as the fact that it will be performed initially in only one center; furthermore, the ICU had a mixed profile of patients, including clinical and surgical patients. Another confounding variable will be the absence of a prior functional status control for physical exercise.

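### Ventilation time is compared by log-rank under intention to treat although entry does not require ventilation, so the comparison is diluted and exposed to chance imbalance in ventilation at entry.

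*Protocol article*

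**What the plan says.** In the protocol article, Intervention outcomes lists as a secondary outcome: "Days with mechanical ventilation and mortality at 28 days after randomization or discharge from the ICU". That sentence gives an end of follow-up but does not say when ventilation days start to count.

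Data analysis then fixes the method: "Kaplan-Meier analysis will be used to estimate ICU LOS, mortality, and mechanical ventilation time", with a log-rank test for the difference between the arms. It names no ventilated subset and closes with a general rule: "All study analyses will be used performed according to the intention to treat".

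Participants sets the entry conditions. Ventilation is not among them. A patient needs "a minimum functional classification of level 1 (i.e. being able to roll in the bed and bridge", and also "the ability to interact with the physiotherapist, determined by at least three positive responses of the following five commands". Excluded are "patients with hospitalization time greater than 72 hours before the start of the study". The limitations paragraph adds that "the ICU had a mixed profile of patients, including clinical and surgical patients".

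Allocation is by simple randomization. The stratified analyses planned in Data analysis use age, initial functional status and APACHE II, not ventilation.

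**The concern.** A time-to-event analysis of ventilation needs patients who are at risk of coming off the ventilator. This trial will enrol some who are not ventilated, and the entry criteria, which ask for bed mobility and response to commands, lean towards such patients.

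Taken together, the named method and the intention-to-treat rule leave two readings:

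- **Never-ventilated patients enter at zero days.** Each is then an event at time zero, which tells us nothing about how fast ventilated patients are liberated.
- **Only patients who were ever ventilated are kept.** The set then depends partly on intubation after randomization, and the analysis is no longer intention to treat.

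Ventilation before randomization (entry is allowed up to 72 hours into the stay) also cannot be changed by treatment, so counting it would add noise.

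At stake is a secondary outcome that the abstract names among the trial's aims. A real effect on liberation could be missed, and a chance difference in who was ventilated at entry would feed directly into the curves.

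**Working it through.** **The plan's own figure.** The article gives no calculation for ventilation time. Its sample size rests on length of stay: a difference of 2.5 days with SDs of 4.1 and 4.5. The mean variance is (16.81 + 20.25)/2 = 18.53. Then n per arm = 2 × (1.96 + 0.84)² × 18.53 / 2.5² = 46.5, so 47 per arm and 94 in total; 94/0.8 = 117.5, so 118. Both figures reproduce.

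**Assumptions.** The share ventilated at entry, v, is not in the article; 10% to 40% is assumed. The hazard ratio of 1.8 for liberation is also assumed. All 118 patients (59 per arm) are taken as analysed.

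**Chance imbalance at entry.** SE of the difference in ventilated share = √(2v(1−v)/59).

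| v | Ventilated per arm | SE | 95% range |
|---|---|---|---|
| 10% | 5.9 | 0.055 | ±11 points |
| 20% | 11.8 | 0.074 | ±14 points |
| 30% | 17.7 | 0.084 | ±17 points |
| 40% | 23.6 | 0.090 | ±18 points |

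**Dilution, by formula.** Ventilated patients contribute about 118v liberation events and log-rank variance V1 ≈ 118v/4. Never-ventilated patients at zero days add V0 ≈ 118v(1−v)/4 at time zero, with no signal about liberation. The expected z is ln(1.8)·√V1 in the ventilated only. In all patients it is multiplied by √(V1/(V0+V1)) = √(1/(2−v)). Power = Φ(z − 1.96), with ln(1.8) = 0.588.

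- v = 20%: z = 0.588 × √5.9 = 1.43, power 30%. All patients: 1.43 × 0.745 = 1.06, power 18%.
- v = 30%: z = 0.588 × √8.85 = 1.75, power 42%. All patients: 1.75 × 0.767 = 1.34, power 27%.
- v = 40%: z = 0.588 × √11.8 = 2.02, power 52%. All patients: 2.02 × 0.791 = 1.60, power 36%.

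This approximation is somewhat optimistic, because late risk sets are small.

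**Dilution, by simulation** (118 patients, never-ventilated = 0 days, hazard ratio 1.8):

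| v | All patients | Ventilated at entry only |
|---|---|---|
| 20% | 17% | 26% |
| 30% | 23% | 36% |
| 40% | 30% | 49% |

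Another set-up (exponential durations with mean 6 days, censored at day 28) gave 12% vs 26%, 22% vs 39% and 29% vs 50%. The direction is stable; individual figures move by a few points. For 80% power at this hazard ratio, 91 liberation events are needed; 118v gives only 24 to 47.

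**Is the test biased?** With no treatment effect, simulated type I error was about 4% to 7%. It was higher (up to about 10%) only at a 10% share, where events are few. Overall, then, randomization largely protects the test. Among trials that happen to have an imbalance of 10 points or more, rejection was 22%, 14% and 13% at shares of 20%, 30% and 40%. That is what exposure to chance imbalance means here: an avoidable component of noise that a baseline adjustment would remove.

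**The case against.** Several points on the other side are fair.

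- **The article never says that never-ventilated patients enter as zero.** It names no population for this outcome; inclusion of all patients is inferred from the general intention-to-treat sentence. A condensed article may leave the at-risk set and time origin to a fuller document. This stands, and a missing rule alone would not be worth raising. What remains is that the method and the population principle that the article does fix fit poorly together when ventilation is not an entry condition.
- **Chance imbalance is already in the p-value.** This stands: type I error is close to nominal, and pre-randomization ventilation is balanced on average.
- **Ventilated patients may not be few.** The five commands need no speech, and surrogate consent is allowed. This stands, and it is why the size is given only as a range.
- **Staying off the ventilator can itself be an effect of treatment**, since patients may be intubated later. This stands. It argues for keeping an all-patient comparison of days beside the liberation analysis.
- **The gain is modest and the outcome secondary.** Power stays low either way, and the primary outcome and its sample size are untouched. This limits the weight of the point but does not remove it, because the better analysis costs almost nothing.

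**Conclusion.** The point holds in a conditional form. With never-ventilated patients at zero days, the planned log-rank comparison is diluted and open to chance imbalance in ventilation at entry. Under the assumed 20% to 40% share and hazard ratio of 1.8, power is about 17% to 30% in all patients against 26% to 49% in those ventilated at entry. The loss shrinks as the share rises and vanishes if everyone is ventilated. The simulations ignore death and intubation after entry.

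A reader might infer two stronger claims, and the article supports neither:

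- **That the result would mainly show who was ventilated at entry.** The part of the variance in ventilation days due to ventilated yes/no is (1−v)/((1−v) + CV²), where CV is the coefficient of variation of days among the ventilated. It is 76% at v = 20% and CV 0.5, but 33% at v = 50% and CV 1.0, and 9% at v = 90% and CV 1.0. The article gives neither quantity.
- **That the test is systematically biased or produces false positives.** The simulated type I error does not show this.

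**What to change.** In Intervention outcomes and Data analysis:

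1. Count ventilation from randomization.
2. Run the time-to-liberation analysis only in patients ventilated at randomization, a set fixed at baseline, with death as a competing event.
3. For all randomized patients, compare ventilation days from randomization to day 28, zeros kept, with the negative binomial model that Data analysis already names. Adjust for ventilated at randomization (yes/no).
4. Report deaths beside that comparison, or use ventilator-free days, so that an early death does not count as a short ventilation time.

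The cost is a change of analysis wording and one baseline item available from the chart; no extra patients are needed. The downside is that the liberation analysis visibly rests on fewer patients and stays low-powered, so it should be presented as an estimate with its confidence interval.

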## Introduction

Physical rehabilitation strategies involving active and progressive mobilization protocols have been recommended for the management of critical illness-related morbidity [1]. The strategies focus on reducing the length of stay in an intensive care unit (ICU LOS), preventing prolonged mechanical ventilation [2], increasing mobility and muscle strength, and extending the days alive out of hospital to 180 days [3] in patients hospitalized in an intensive care unit.

Despite the recommendation of early mobilization for critically ill patients, the effects of mobilization are inconclusive. Serious risk of bias, imprecision, and heterogeneity of individual study designs and intervention protocols hamper the ability to achieve a precise and accurate estimate of the effect size and decrease the quality of evidence [4]. Few published randomized clinical trials (RCTs) have adequately described the dose and intensity of the protocols used [4,5]. There is considerable variability in the results of clinical trials evaluating early mobilization [6]. Tipping et al. [3] reported that there is no consistent effect of active mobilization on ICU LOS. According to the authors [3], several studies did not separate the LOS for survivors and non-survivors and the limitations identified in the individual RCTs prevent the pooling of results for meta-analysis.

It is well documented that the exercise dose is a determining factor for the results of exercise programs. Variables such as intensity, execution time and rest, number of repetitions, and progression may influence strength gain and cardiorespiratory capacity [7,8]. Despite the variety of progressive active mobilization protocols, the optimal training scheme has not yet been defined [3,4]. The most important factor influencing outcomes such as LOS, strength, and function may be the addition of a training dose control protocol based on the major international protocols [5] and involving variables of intensity, frequency, number of repetitions, rest time, and progression scheme.

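### ICU stay and ventilation time are analysed without treating ICU death as a competing event, so early deaths can pass for short stays

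*Protocol article*

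**What the plan says.** All references are to the protocol article.

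- **Intervention outcomes:** "The primary outcome will be the length of stay in the ICU". Days on mechanical ventilation and mortality are separate secondary outcomes. No rule says how a stay or a ventilation period ended by death is scored.
- **Data analysis, time-to-event methods:** "Kaplan-Meier analysis will be used to estimate ICU LOS, mortality, and mechanical ventilation time, and a log-rank will be used to assess" the difference between groups. One sentence covers all three outcomes, with no event or censoring definition for any of them.
- **Data analysis, comparison of means:** "analysis of variance (ANOVA) will be used to compare the mean differences of the variables", with a rank-based fallback if the data are not normal. Mean and median differences with 95% confidence intervals are also planned.
- **Data analysis, analysis set:** "All study analyses will be used performed according to the intention to treat".
- **Sample size calculations:** the target is a "mean difference in the length of hospital stay of 2.5 days", from 12.7 (SD 4.1) v 15.2 (SD 4.5) days. Then: "After adjusting 20% for missing, death, loss to follow-up, and withdrawals, the corrected sample was 118 subjects".
- **Introduction:** a cited meta-analysis is reported as finding that "several studies did not separate the LOS for survivors and non-survivors".
- **Participants:** only patients with predicted mortality above 50% are excluded, so some deaths must be expected.

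**The concern.** Death in the ICU ends the stay and makes discharge alive impossible. It is neither a good short stay nor ordinary loss to follow-up. A method that does not separate the two ways of leaving the ICU mixes the effect on recovery with the effect on mortality.

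The error can go either way. If the intervention arm had more early deaths, its stays would look shorter and the trial could report a benefit that does not exist. If the intervention prevented early deaths, the patients saved would add long stays and hide a real benefit. Ventilation time has the same weakness, because death on the ventilator ends the count of days.

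The Introduction itself reports, as a weakness of earlier trials, that survivors' and non-survivors' stays were not separated. The analysis section does not then make that separation.

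**Working it through.** **1. The plan's own figure.** The pooled variance is (4.1² + 4.5²)/2 = (16.81 + 20.25)/2 = 18.53. Per arm, n = 2 × 18.53 × (1.960 + 0.842)² / 2.5² = 46.5, rounded up to 47, so 94 in total. Then 94/0.8 = 117.5, rounded up to 118 (59 per arm). The stated sample size reproduces. It compares mean stays and makes no separate provision for how deaths are scored.

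**2. What each reading of the stated methods does with a death.**

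| Reading | Effect of an ICU death |
|---|---|
| Mean difference in raw stay | Counts as a short stay if early |
| Log-rank, any exit is the event | Counts as an exit, the same as discharge alive |
| Log-rank, deaths censored | Valid cause-specific test of live discharge |
| One minus Kaplan-Meier, deaths censored | Overstates the proportion discharged alive |

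On the last row, suppose 20% die and all survivors eventually leave. The Kaplan-Meier complement climbs to 100%, but only 80% were discharged alive.

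**3. Shift in the mean, no true effect.** Assumptions, not in the documents: deaths at a mean of day 6; survivors in both arms stay 15.2 days on average. Shift = mortality difference × (15.2 − 6).
- 20% v 10%: 0.10 × 9.2 = 0.92 day, which is 37% of the 2.5-day target.
- 10% v 5%: 0.05 × 9.2 = 0.46 day.

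**4. False finding of a shorter stay** (simulation, 59 per arm, no true effect, nominal 2.5% in that direction).

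| Mortality, intervention v control | t-test on raw stay | Log-rank, all exits |
|---|---|---|
| 20% v 10% | about 15% | about 9% |
| 10% v 5% | about 7% | 4–5% |
| 10% v 10% | about 2.5% | about 2.5% |

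With deaths censored, the log-rank stays at 2.5–3.0% when death is unrelated to the stay a patient would otherwise have had. If patients heading for longer stays die more often, it rises to 4–14% as intervention mortality goes from 15% to 30% against 10% in control. This is why the result for death must stand beside it.

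**5. Lost power, true 2.5-day benefit in survivors.** With mortality of 10% (intervention) v 20% (control) and deaths around day 6:
- Intervention mean: 0.9 × 12.7 + 0.1 × 6 = 12.03 days.
- Control mean: 0.8 × 15.2 + 0.2 × 6 = 13.36 days.
- Observed difference: 1.33 days instead of 2.5.

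Simulated power is about 28–31% (t-test), 55–58% (log-rank on all exits) and 83% (log-rank for live discharge). The ranges reflect simulation details.

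**6. Sensitivity.**
- Same mortality, deaths around day 12: t-test 61%, all-exit log-rank 70%.
- Mortality 5% v 10%, day 6: all-exit log-rank 75%.
- Mortality 10% in both arms: all-exit log-rank 81%, against 85% with deaths censored.
- Mortality 15% in both arms: the mean difference is 0.85 × 2.5 = 2.1 days and t-test power is about 62%.

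**The case against.** The case on the other side is substantial, and much of it stands.

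- **The log-rank test is not wrong in itself.** A reader might infer that every named method mishandles death. The documents do not support that. A log-rank test with live discharge as the event and deaths censored fits the stated wording, and it is the test recommended below. For the test alone, the gap is an unstated rule, which a full analysis plan might supply.
- **Mortality is not ignored.** It is a named secondary outcome with its own Kaplan-Meier and log-rank comparison, so excess deaths would be visible to a careful reader. They would still not enter the analysis of stay.
- **The 20% allowance does not define an analysis set.** A reader might infer from the listing of death there that only survivors will be analysed, contrary to intention to treat. The sentence only enlarges the sample, so that inference is not secure. It leaves the treatment of deaths unclear and no more.
- **ANOVA on ICU stay is an inference.** It rests on the generic reference to the variables and on the sample size for means. ICU stay is named only with Kaplan-Meier and log-rank, so the t-test figures carry less weight than the all-exit log-rank figures.
- **Kaplan-Meier with death as an exit** does describe time spent in the ICU. That is a coherent quantity, but it does not measure recovery.
- **The size depends on chosen death rates and timing.** The 50% limit on predicted mortality is a cap, not an expected rate, and entrants must be able to cooperate and move in bed.

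What survives is that the article fixes Kaplan-Meier for ICU stay and ventilation time. With no competing-event treatment, that estimate either merges deaths with discharges or overstates live discharge. This is a stated method, not only an omitted detail.

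**Conclusion.** The concern holds in limited form. The stated analysis of ICU stay and ventilation time does not treat ICU death as a competing event, and on the natural reading of raw stay an early death counts as a short stay.

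The false benefit needs a mortality difference between arms. It is material at 20% v 10%, small at 10% v 5%, and absent when mortality is equal. Power is lost in all the scenarios examined, but less so with equal mortality or later deaths. All of these figures rest on assumed death rates and timing, because the documents give none. On the same simulated data, power ran from about 28% to 83% according to a rule the article does not state. That is reason enough to fix the rule before the data are seen.

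**What to change.** - **Primary event:** define it as discharge alive from the ICU, in all randomised patients, with ICU death as a competing event.
- **Display:** replace the Kaplan-Meier curves for stay with Aalen-Johansen cumulative incidence of live discharge and of death, by arm.
- **Test:** use the cause-specific log-rank test or Cox model for live discharge, and always report the cause-specific result for death beside it.
- **Ventilation:** use the same competing-event method, or ventilator-free days to day 28 with death scored 0. The second option needs ventilation and vital status to day 28. The article lists these outcomes at 28 days or at ICU discharge, so confirm that follow-up continues after discharge before choosing it.
- **Sample size text:** state that deaths counted within the 20% allowance remain in the intention-to-treat analysis.

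The cost is mainly wording. The primary analysis needs only the date and manner of leaving the ICU, and the total of 118 need not change on this account. The downside is a result that is slightly harder to explain than a difference in mean days.
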